## Abstract

**Background:**

Cancer patients transitioning to survivorship after completing cancer treatments need psychosocial interventions to manage stressors such as anxiety, depression, and fear of cancer recurrence. Mindfulness-based interventions (MBIs) are effective for treating these symptoms; however, cancer survivors are often unable to participate in face-to-face interventions because of difficulties such as work and family commitments, treatment-related side-effects, scheduling conflicts, and geography. Smartphone app–based MBIs are an innovative way to deliver psychosocial cancer care and can overcome several such difficulties, since patients can participate at their own convenience.

**Objective:**

The SEAMLESS (Smartphone App–Based Mindfulness Intervention for Cancer Survivors) study aims to evaluate the efficacy of a tailored app-based mindfulness intervention for cancer survivors (the *Am* Mindfulness-Based Cancer Survivorship—MBCS—Journey) for treating (1) symptoms of stress (primary outcome), as well as (2) fear of cancer recurrence, anxiety, depression, fatigue, and overall physical functioning (secondary outcomes). This is the first Canadian efficacy trial of a tailored mindfulness app intervention in cancer survivors.

**Methods:**

This is a randomized waitlist-controlled trial, which will evaluate the effectiveness of *Am* MBCS for impacting the primary and secondary outcomes in cancer survivors who have completed all their cancer treatments. Outcomes will be assessed using web-based surveys with validated psychometric instruments at (1) baseline, (2) mid-intervention (2 weeks later), (3) immediately postintervention (4 weeks), (4) 3 months postbaseline, (5) 6 months postbaseline, and (6) 12 months postbaseline. The waitlist group will complete all assessments and will cross over to the intervention condition after the 3-month assessment. In addition, data will be obtained by the smartphone app itself, which includes users’ engagement with the app-based intervention, their emotional state (eg, angry and elated) from a user-inputted digital emotion-mapping board, and psychobiometric data using photoplethysmography technology.

**Results:**

The study received ethics approval in September 2018 and recruitment commenced in January 2019. Participants are being recruited through a provincial cancer registry, and the majority of participants currently enrolled are breast (44/83, 53%) or colorectal (17/83, 20%) cancer survivors, although some survivors of other cancer are also present. Data collection for analysis of the primary outcome time-point will be complete by September 2019, and the follow-up data will be collected and analyzed by September 2020. Data will be analyzed to determine group differences using linear mixed modelling statistical techniques.

**Conclusions:**

Cancer care providers are uncertain about the efficacy of app-based mindfulness interventions for patients, which are available in great supply in today’s digital world. This study will provide rigorously evaluated efficacy data for an app-based mindfulness intervention for cancer survivors, which if helpful, could be made available for psychosocial care at cancer centers worldwide.

**Trial Registration:**

ClinicalTrials.gov NCT03484000; https://clinicaltrials.gov/ct2/show/NCT03484000

**International Registered Report Identifier (IRRID):**

DERR1-10.2196/15178

## Introduction

### Background

Previous research suggests that cancer survivors in Canada have several unmet psychosocial needs after completing treatments, which differ from patients newly diagnosed or undergoing treatment [1]. Almost half of all cancer survivors experience symptoms from late and long-term effects of treatments such as fatigue, pain, and distress [2]. Concurrently, they must deal with psychosocial stressors such as anxiety, depression, uncertainty about the future, and fear of cancer recurrence as they transition back to their previous roles and responsibilities at home and in the workplace; these factors can impair their quality of life, performance at work, and their ability to contribute to society [3,4]. Furthermore, the number of cancer survivors in Canada continues to rise due to rapid advances in early detection and treatments for cancer in an aging population. The most recent data suggest there are over 800,000 Canadians living with a history of cancer diagnosed in the previous 10 years [5]. Moreover, these numbers are expected to increase since survival data indicate 60% of Canadians with the top 4 most common cancer diagnoses are expected to survive at least 5 years postdiagnosis [6].

Similar trends of rising numbers of cancer survivors have been reported in the United States, and the world over [2]. Thus, cancer survivors globally can benefit from innovative interventions that address their unique psychosocial needs during survivorship. A growing body of evidence supports the efficacy of a range of mind-body therapies in alleviating these and other symptoms in cancer patients and survivors [7]. Among these therapies, mindfulness-based interventions (MBIs) have demonstrated significant efficacy in impacting psychosocial and physical health in the cancer population, such as the Mindfulness-Based Cancer Recovery (MBCR) program, a 9-week group behavioral treatment program that trains participants in mindfulness techniques through meditation and gentle movement practices [8].

The investigators on this research team LC and MS have studied MBCR for the past three decades and have tested its efficacy in a range of studies and groups of people with cancer, with success in impacting a range of biological and psychosocial outcomes including, but not limited to, symptoms of stress, quality of life, and mood disturbance [8-10]. This body of work on MBCR has spanned basic mechanistic research to clinical trials and implementation science. Most research studies of this nature have tested MBIs such as MBCR when delivered face to face in a group-based setting, although a variety of online-based and digitally adapted MBIs are now available to patients through smartphone apps [11]. Mobile app–based MBIs for cancer patients and survivors allow for considerable flexibility and appeal, especially since they eliminate the need for travel time and problems due to scheduling conflicts [11,12].

### Digital Health Interventions in Cancer Care

One of the most significant social and economic changes in the modern world has been the use of computer technology and the internet. Recent data indicate that 76% of Canadians now own a smartphone device with data connection across all demographic groups, and the numbers are projected to increase consistently [13,14]. The popularity of this medium is of great interest for health practitioners, researchers, and policy makers considering the wide-ranging capabilities of smartphone devices. In the field of cancer care, reviews of internet and smartphone app–based interventions for cancer patients and survivors have suggested that cancer patients find these interventions to be highly acceptable and feasible [15,16]. Furthermore, psycho-oncology researchers have advocated for more research with psychosocial interventions that can be delivered using the internet and smartphone apps in the cancer population [15-17].

### Benefits of App-Based and Online Mindfulness Interventions

App-based and online mindfulness-based interventions circumvent problems with traditional face-to-face delivery of MBCR such as work schedules, conflicts with other appointments, lack of childcare, and residing far from treatment centers in remote locations. Another potential benefit of app-based and online mindfulness interventions in cancer care is the considerable cost savings for the health care system without compromising on the quality of care, as online and artificial intelligence technologies can simulate the real-world experiences; in addition, studies have shown these interventions to be highly feasible and acceptable. For example, authors LC and MS conducted a feasibility trial of online MBCR, which found that more than 80% of participants completed the online MBCR program, and a 10% response rate to recruitment letters was achieved (the target was 5%) [18]. Also, recent systematic reviews and meta-analyses of app-based mindfulness interventions in the cancer population report high feasibility and acceptability; albeit engagement is an important variable to consider for intervention success [16,19,20].

However, while there are hundreds of commercially available mindfulness training apps, eg, *Headspace*, *Calm*, and *10% Happier* [21,22], only *Headspace* has been customized for cancer patients and been scientifically evaluated [21]. Data from a randomized waitlist-controlled trial and a prospective cohort study of *Headspace* have demonstrated good overall efficacy for improving outcomes such as quality of life and anxiety in women diagnosed with breast cancer [21,23]. However, the overall science of app-based MBIs is still in its early stages and far from achieving consensus about efficacy of intervention platforms, as well as understanding mechanisms of action [12,17]. For example, this is demonstrated by a randomized trial of *Headspace* with college students that reported no effects for the mindfulness component of *Headspace’s* app-based program [24].

Furthermore, *Headspace’s* audio content is exclusively voiced and delivered by the app’s founder in a monologue format [25]. This approach may not connect with all cancer patients and survivors, considering the importance of the patient-psychotherapist relationship in determining the success of any psychotherapeutic practice [26,27]. Also, cancer patients and survivors are more inclined to accept and utilize content created and delivered by clinical experts, for reasons such as source credibility and condition-specific content [28-30]. The research team for this study was interested in developing an app-based MBI for cancer survivors that simulated the interactive dialogic approach used in the MBCR program. The research team chose to evaluate the *Am Mindfulness* app as it could potentially address the gaps in the design and delivery of app-based MBIs for the cancer population.

*Am Mindfulness* is a readily editable digital platform with audio and visual capabilities and its content can be updated and modified with automatic app updates. *Am Mindfulness* was developed and is maintained by Mobio Interactive (MI) Inc. [31], a Canadian technology company based in Toronto, Canada, cofounded by MT and BS; user data are maintained on secure servers in Canada and meet security and Health Insurance Portability and Accountability Act privacy standards required for medical data. The name for *Am Mindfulness*, referred to simply as, *Am,* and pronounced “ahm” was chosen by MI for several reasons. First, “am” is the present tense of the verb “to be,” which is a linguistic embodiment of mindfulness given the high emphasis that mindfulness practices place on observing the present moment. Second, because of how “Am” is pronounced, it sounds similar to both the word for “soul” in French (“âme”) and the chant “ohm” used in ancient meditative practices from India. Finally, the name “Am” is relatively simple and less likely to bias individuals on the app’s purpose or offering in the way that names for other meditation-focused apps such as “Calm” or “Smiling Mind” may.

The design of *Am Mindfulness* allows for considerable flexibility with delivering content in real time through the “Journeys” app feature. Each app-based “Journey” involves a sequence of custom audio tracks, visuals with text and in-app exercises designed with a particular objective, eg, mindful survivorship. The content of a “Journey” can be seamlessly introduced and refined for a patient population in real time. MI describes their major motivation for creating the “Journeys” feature in *Am Mindfulness* as their commitment to create and deliver diverse content voiced over by clinical experts, in addition to mindfulness practitioners, to address the needs of specific patient populations [32]. Evidence from a recent randomized trial with a prerelease version of the *Am Mindfulness* app (called *Wildflowers*) has demonstrated efficacy evidence for reducing anxiety in college students before a stressful event of an examination [33].

In this project, the *Am* Mindfulness-Based Cancer Survivorship (MBCS) journey was developed and recorded in the voices of MBCR program facilitators LC and MS. Several audio tracks in the *Am* MBCS journey have a dialogue and interaction between LC and MS, who are clinical psychologists and leading experts on mindfulness-based cancer recovery, having developed and scientifically evaluated the MBCR program together for over 20 years. Details of the *Am* MBCS journey are described in the *Intervention* section and illustrated in Figure 1. In this study, we intend to test the efficacy of the *Am* MBCS Journey, referred to hereon as *Am* MBCS, to reduce stress in cancer survivors. As secondary objectives, we will investigate the feasibility of recruitment as well as the usability of the app and in-app data on specific usage patterns.

**Figure 1 figure1:**
[figure not shown]
The Mindfulness Based Cancer Survivorship (MBCS) Journey Contained within *Am*. (A) Navigation menu. (B) Core audio content (C) In-app exercises.

## Methods

### Study Design

The study is a two-armed randomized waitlist-controlled design with 1:1 allocation to treatment (immediate *Am* MBCS app group) or control (waitlist usual care) arms, with assessments at six time points: (1) baseline, (2) mid-intervention (2 weeks later), (3) immediately postintervention (4 weeks), (4) 3 months postbaseline, (5) 6 months postbaseline, and (6) 12 months postbaseline. A detailed study flowchart is shown in Figure 2. This is an open-label trial, as blinding to interventions is most often not possible in psychosocial intervention research.

**Figure 2 figure2:**
[figure not shown]
SEAMLESS Study Flow Chart. Includes study design, stage, and all time points of data collection for study assessments.

### Participants

Cancer survivors with any type of cancer who have completed their active treatments at least 2 weeks before recruitment in this study will be included. Inclusion criteria are intentionally broad to be pragmatic and improve generalizability to the real world. Refer to Table 1 for detailed rationale for each inclusion and exclusion criterion.

**Table 1 table1:** Inclusion and exclusion criteria.

Criteria		Rationale and notes
**Inclusion**		
	(1) Men and women over the age of 18 years	Both men and women are included to broaden the generalizability of results and allow sex comparisons. All participants must be adults.
	(2) Completed all cancer treatments 2 weeks before enrollment	A brief period of time is required for patients to recuperate after their last treatment, before starting a new intervention.
	(3) Access to a smartphone with data connection	Patients will require access to a smartphone to participate. The study team will communicate primarily by phone, text message, and email. In case some patients’ do not have a data plan or an insufficient data plan with their smart phone, we will pay for their data connection (up to 0.5 GB/month).
	(4) Willing to give time for mindfulness practice	Patients need to have the motivation to devote approximately 20 to 30 min daily, which is equal to 5 to 7 sessions a week over the course of 1 month to do the mindfulness meditations and practices.
	(5) Sufficient ability to speak and read English	The audio lectures and meditations and assessments will be conducted in English, so participants must be able to understand the audio and fill out the questionnaires.
	(6) Willingness to be randomized into immediate or waitlist groups and complete all assessments	People must be comfortable with potentially having to wait to get access to the app-based program for another 3 months, as well as be motivated to give 30 to 40 min of their time to complete the online survey assessments.
**Exclusion**		
	(1) Suffering from current major depressive disorder, or other psychiatric disorder (self-reported) that would interfere with the ability to participate	Evidence indicates that participants with active psychological disorders should be first treated for these problems individually, before engaging in experimental mental health and meditation programs of this nature, which are not intended to treat these disorders.
	(2) Currently engaging in mindfulness meditation one or more times per week	To ensure sample homogeneity, the study will include participants who are NOT currently practicing mindfulness, using an app or otherwise. However, this would not exclude everyone who may have casually experimented with the aforementioned interventions in the past.
	(3) Cognitive impairment that would interfere with completing questionnaires or the intervention; <6 on the Brief Screen for Cognitive Impairment (BSCI) [3]	People require enough cognitive capacity to complete the questionnaires, navigate and listen to the app and complete homework independently. The BSCI only rules out those with significant cognitive impairment and will not exclude those with the milder cognitive impairment associated with cancer-related “brain fog.”

### Recruitment

Potential participants will be recruited at a comprehensive cancer center in Western Canada from a Provincial Cancer Registry.

#### Alberta Cancer Registry

The Alberta Cancer Registry (ACR) is a population-based registry, established in 1942, that records and maintains data on all new cancer cases and cancer-related deaths occurring in the province of Alberta. The registry records information about the type of cancer and cancer treatments, as well as personal information, such as name, date of birth, sex, provincial health care number, and postal code. The ACR will contact all potential participants on behalf of the research team with a study information letter with the research team’s contact information. Potential participants will include patients diagnosed with any type of cancer, who completed their treatments at least 2 weeks prior and who reside outside the Calgary metropolitan region. The geographical criteria were chosen to access cancer survivors in urban and rural areas of Alberta that are distant from the University Health Center, as most mindfulness-based programs and studies have been mainly accessible for residents of the Calgary metropolitan region due to its proximity to the University Health Center. The ACR’s method of contact ensures patient privacy and provides patients the choice to participate in the study. Interested participants will then contact the research team, and then are further screened for inclusion criteria.

### Sample Size

In previous studies with face-to-face group MBCR, we have observed medium effects for symptoms of stress (measured by the Calgary Symptoms of Stress Inventory [C-SOSI]) as the primary outcome and expect similar effects in this study. Also, recent meta-analyses of MBIs and psychosocial stress outcomes have demonstrated a similar medium standardized effect size of Cohen *d*=0.5 for stress [34]; also, most MBI studies collect their primary outcome at 3 months postbaseline as most mindfulness interventions span 6 to 10 weeks [7,34]. For this study, we therefore used a medium effect size (*f*=0.25) to conduct an a priori sample size calculation using the software G*Power 3.1.9.3 developed and maintained by researchers at Heinrich Heine University Düsseldorf [35]. The other parameters for estimating the sample size included, a standard type-1 error rate, α=.05, and a low risk of type-2 error, power (1-β)=.95, to detect interaction effects between time points (baseline and 3 months postbaseline) and group (intervention and control) using a repeated measures analysis of variance with correlation among repeated measures assumed to be 0.5 and nonsphericity correction ε=1. The total required sample size reported by G*Power was 54 participants to detect such an interaction effect.

In addition, based on our previous experience with online and in-person MBI trials and previous app-based studies [10,18,20,34,36], we assumed approximately 20% attrition and 10% to 15% probability of missing data. Therefore, we oversampled for this study accordingly. Hence, the final total sample size we aim to recruit in this study is N=74, with n=37 in the immediate intervention arm and n=37 in the waitlist control arm. Please refer to Figure 2 for the study flowchart that describes estimated sample size calculations at each assessment.

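### The sample size of 54 has 95% power for a 1.0 SD difference in change, not for the cited d=0.5, for which power is about 44%

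*Protocol article*

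**What the plan says.** The Sample Size section of the protocol article gives two grounds for the expected effect: medium effects on the C-SOSI in the team's earlier face-to-face studies, for which no number is given, and meta-analyses reporting "a similar medium standardized effect size of Cohen *d*=0.5 for stress". It then states: "we therefore used a medium effect size (*f*=0.25) to conduct an a priori sample size calculation". The remaining inputs are "a standard type-1 error rate, α=.05", "a low risk of type-2 error, power (1-β)=.95", and "correlation among repeated measures assumed to be 0.5 and nonsphericity correction ε=1". The target of the calculation is "to detect interaction effects between time points (baseline and 3 months postbaseline) and group (intervention and control) using a repeated measures analysis of variance". The result is: "The total required sample size reported by G*Power was 54 participants to detect such an interaction effect".

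To allow for about 20% attrition and 10% to 15% missing data, the recruitment target is raised to 74, or 37 per arm. The Results section reports that 83 participants have consented and enrolled.

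**The concern.** Cohen's d and Cohen's f are different scales, and the relation between them depends on the contrast tested. For a one-way comparison of two independent means, f=d/2, so d=0.5 corresponds to f=0.25. The calculation here is for a 2x2 within-between interaction, where that relation does not hold. The protocol ties its f to the cited d with the word "therefore", and it nowhere argues that a 1.0 SD difference in change is expected.

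The power claimed for the primary outcome is at stake. Readers told that the trial has 95% power for a medium effect would take a non-significant result as good evidence against such an effect. If the real power for d=0.5 is near one half, the trial is about as likely to miss that effect as to find it.

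**Working it through.** **Inputs (Sample Size section).** k=2 groups, m=2 time points, alpha .05, power .95, rho=0.5, epsilon=1, f=0.25, cited d=0.5, N=54 before losses and 74 after. The 83 enrolled come from the Results section.

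**1. Reproduce the stated N.** For the within-between interaction in a repeated-measures ANOVA:

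- lambda = f² · N · m / (1 − rho), with df1 = (k−1)(m−1) = 1 and df2 = (N−k)(m−1) = N−2
- N=54: lambda = 0.0625 · 54 · 2 / 0.5 = 13.5 on F(1, 52), power 0.9501
- N=52: lambda = 13.0, power 0.942

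So 54 is the smallest even N that reaches 95%, as stated. If the factor m/(1−rho) is left out, the same f would need 210, which shows that the formula above is the one used.

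**2. What f=0.25 means in this test.** The four interaction deviations are +a, −a, −a, +a, and f is their root mean square divided by sigma, so f = a/sigma. The difference in change between arms is 4a. Hence

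- f = (difference in change, in SD) / 4
- f=0.25: difference in change 4 · 0.25 = 1.0 SD
- difference in change 0.5 SD: f = 0.5/4 = 0.125

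As a check, the t test on change scores has squared noncentrality delta² · N / (8(1 − rho)). Setting this to 13.5 with N=54 and rho=0.5 gives delta² · 54/4 = 13.5, so delta = 1.0 SD.

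At rho=0.5 the SD of change is sqrt(2(1 − 0.5)) = 1.0 outcome SD. It therefore makes no difference whether d is scaled by the SD of the outcome or of the change.

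**3. Power for d=0.5 (f=0.125), other inputs as stated.**

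| Evaluable N | lambda = 0.015625 · N · 4 | Power |
|---|---|---|
| 54 | 3.375 | 43.8% |
| 74 | 4.625 | 56.4% |
| 83 | 5.1875 | 61.4% |

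A simulation of 40,000 trials with 27 per arm gave 44.0% for a 0.5 SD difference in change and 95.0% for 1.0 SD. The rows for 74 and 83 assume no losses.

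**4. N required for d=0.5 on the same test.** 128 for 80% power, 172 for 90% and 210 for 95%, all evaluable.

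**5. Smallest difference in change detectable with 95% power.** 1.00 SD at N=54, 0.85 SD at 74 and 0.80 SD at 83.

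**6. Sensitivity to assumptions the protocol does not make (d=0.5, N=54).** Change-score power is 33% at rho=0.3, 64% at rho=0.7 and 81% at rho=0.8. A baseline-adjusted analysis at rho=0.5 gives about 55% at N=54 and 69% at N=74. The change-score test reaches 95% at N=54 only with a correlation close to 0.9.

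**The case against.** The protocol shows no conversion from d to f. It may simply have matched Cohen's verbal label, since both 0.5 and 0.25 are called medium, and the effect seen in the team's own C-SOSI studies is not quantified. Nor does the article say whether the meta-analytic d is a between-group, pre-post or change-score effect. These points stand as cautions about how the figure arose, but they do not alter what f=0.25 means in the test named. The only numerical effect cited is 0.5. Even if that were a pre-post gain set against no change in controls, the difference in change would be 0.5 SD.

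A second objection is that the planned analysis is a linear mixed model and that another correlation or baseline adjustment would raise power. This softens the size of the gap. However, the protocol fixes rho at 0.5 and plans to test the same group-by-time interaction. At the evaluable number of 54, baseline adjustment at that correlation, or a correlation of up to 0.8 on the stated test, still falls short of 95%.

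It is also fair that the figures at 74 and 83 are ceilings. The protocol expects losses, and because consent precedes the baseline survey and randomization, 83 need not be the number randomized. Finally, the software was used correctly and the target had already been reached. The fault lies in the effect size entered, and the remedy is confined to the text.

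**Conclusion.** The concern holds. The claimed 95% power applies to a 1.0 SD difference in change, which the protocol neither cites nor justifies. For the cited d=0.5, power is about 44% at the planned evaluable number. The type II error risk for that effect is thus about 56% (1 − 0.438), against the stated 5%. Recruiting to 74 does not close the gap, because 56% power is the no-loss ceiling there.

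These figures rest on reading d=0.5 as the between-arm difference at 3 months with equal baselines (equivalently, in change), on the protocol's own rho of 0.5, and on the two-point interaction test it names. Other plausible correlations move the figure at N=54 between 33% and 64% (rho 0.3 to 0.7).

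**What to change.** Restate the calculation in the Sample Size section, for example: 54 evaluable participants give 95% power for a between-group difference in change of 1.0 SD (f=0.25 for the interaction); for d=0.5 (f=0.125) power is about 44% with 54 evaluable and 56% with 74.

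Add the difference that the enrolled number can detect with 95% power: 0.85 SD if 74 are evaluable, 0.80 SD if 83 are. State that a non-significant primary result will be interpreted from the confidence interval and not as showing the absence of a medium effect. If the authors do expect a 1.0 SD difference in change, they should say so and justify it.

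The cost is a few sentences and a less favourable power statement. Recruitment, analysis and the type I error rate are unchanged.
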